## Abstract

**Background:**

Cancer-related fatigue (CRF) is a common and often long-lasting symptom for many breast cancer survivors. Evidence for its management is scarce. However, the Traditional Chinese Medicine (TCM) *Shu Gan Jian Pi* (SGJP) granules is an effective and practical therapy for CRF.

**Methods/Design:**

We will conduct a multicenter, randomized, double-blind, placebo-controlled clinical trial to determine whether the SGJP granules can effectively manage CRF. Breast cancer survivors experiencing fatigue within 5 years of primary treatment completion will be enrolled and randomly assigned to Group S (SGJP) or Group P (placebo). The primary outcome measures will include Revised Piper Fatigue Scale score. Outcome measures will be collected at baseline and at weeks 2, 4, and 8.

**Discussion:**

This study’s findings may contribute to the development of an effective intervention for CRF.

**Trial registration:**

Current controlled trials ISRCTN12702489, 14 August, 2013.

SGJP granules can relieve the syndrome; SGJP is composed of six herbs including *Radix astragali* (*Huang Qi*), *Radix bupleuri* (*Chai Hu*), *Radix angelicae alba* (*Dang Gui*), and three other herbs. The action of *Radix astragali* (*Huang Qi*) is to replenish *qi*. That of *Radix bupleuri* (*Chai Hu*) is to disperse the stagnated liver-*qi*. Four other herbs have the same actions. Many patients in China turn to TCM with the complaint of fatigue after cancer treatment. One study reported that TCM demonstrated the ability to relieve CRF [8]. We have attempted to treat CRF in clinical practice without success. Although SGJP granules have demonstrated positive effects on relieving CRF, rigid validation using a randomized controlled trial remains the best way to examine the effects of SGJP in patients.

## Methods/Design

### Study design

This study will use a two-group multicenter, randomized, double-blind, and placebo-controlled clinical trial design in which participants will receive either enhanced TCM or placebo. We will enroll 118 patients with breast cancer. Participants will be recruited from three centers: Beijing Hospital of Traditional Chinese Medicine, Beijing Cancer Hospital, and People’s Hospital of Beijing Da Xing District. The study schema and estimated recruitment numbers are presented in Figure 1. Randomization will be used to allocate patients to groups subjected to a 4-week treatment period and a 4-week follow-up period. Four visits will be scheduled for each patient: baseline and weeks 2, 4, and 8.

**Figure 1 Fig1:**
[figure not shown]
Flow of patients through the trial. 1. RPFS: Revised Piper Fatigue Scale. 2. ECOG-PS: Eastern Cooperative Oncology Group Performance Status. 3. SRSS: Self-Rating Scale of Sleep. 4. HADS: Hospital Anxiety and Depression Scale. 5. Safety assessment: routine blood test, routine feces test, routine urine test, liver and kidney function tests and electrocardiogram.

### Ethical issues

The study received ethical approval from the Research Ethical Committee of Beijing Hospital of Traditional Chinese Medicine Affiliated with Capital Medical University (number 201338) and registered with the International Standard Randomized Controlled Trial Number Register (ISRCTN 12702489). Patients willing to participate will sign a consent form prior to participating.

### Setting and patients

The study will include breast cancer patients with the complaint of moderate to severe fatigue. Patients will be screened for fatigue using the Revised Piper Fatigue Scale (RPFS) to identify those with significant fatigue. Table 1 will show the detailed eligibility and exclusion criteria. Recruitment will occur at three centers in Beijing: Beijing Hospital of Traditional Chinese Medicine, Beijing Cancer Hospital, and People’s Hospital of Beijing Da Xing District.

**Table 1 Tab1:** **Eligibility criteria for the randomized clinical trial**

Inclusion criteria	
1	Patients have definite outpatient pathologic diagnosis of breast cancer
2	Eligible patients had completed chemotherapy and/or radiotherapy at least 1 month and mastectomy within 5 years
3	Stage I to III breast cancer with no evidence of recurrence and metastasis
4	Eastern Cooperative Oncology Group Performance Status 0 to 2
5	Traditional Chinese Medicine (TCM) syndrome is differentiated as liver depression and spleen deficiency
6	Anticipated survival time exceeds 6 months
7	Eligible patients have no plan to receive chemotherapy and/or radiotherapy during the study
8	Revised Piper Fatigue Scale score ≥ 4
9	Provided signed informed consent before enrollment
Exclusion criteria	
1	Complicated by serious diseases of heart, liver and kidney, immune and hematopoietic systems
2	Children and pregnancy
3	Receiving active treatment for anemia with erythropoietin or blood transfusions
4	Using steroids to cure cancer-related fatigue
5	Diagnosed with depression, mental disease or cognitive impairment
6	Allergic to a Chinese herbal compound

### Intervention

If patients meet the inclusion criteria, they will take a randomly generated number to the pharmacy and the pharmacist will give them SGJP or placebo in a package containing either 15.75 mg medication or dextrin (90%) and *Herba pogostemonis* (10%). Patients will take one package twice daily. The intervention period will be over 4 weeks. After 4 weeks on the prescribed medication, the patients will stop taking SGJP or placebo for another 4 weeks and then undergo the clinical evaluation.

The intervention group treatment is composed of six herbs including *Radix astragali* (*Huang Qi*), *Radix bupleuri* (*Chai Hu*), *Radix angelicae alba* (*Dang Gui*), and three other herbs. The ingredients of SGJP cannot be disclosed because the formula is currently being patented. The control group formulation includes dextrin (90%) and *Herba pogostemonis* (10%). The study medicine was made by Beijing Tcmages Pharmaceutical Co., LTD, Beijing, China. Based on the infrared fingerprint spectrum techniques and Good Manufacturing Practice**s** (GMP) full range management, this company can guarantee the consistency of granule composition.

### Assessment

#### Primary outcome measure

*Revised Piper Fatigue Scale* (RPFS), a multidimensional assessment tool that subjectively measures the level of fatigue of patients with cancer, has been widely used in research. It consists of 22 items, each rated on a visual analog scale with a score ranging from 0 (least) to 10 (most). The items are divided into four dimensions: severity, affective meaning, sensory, and cognition [9].

#### Secondary outcome measure

*Eastern Cooperative Oncology Group Performance Status* (ECOG-PS) is a scale to evaluate performance status. It is based on five levels [10].

*The Self-Rating Scale of Sleep* (SRSS) is a frequently-used instrument in China that consists of 10 items that measure sleep quality. Each item is rated on a scale of 1 (best status) to 5 (worst status) [11].

*The Hospital Anxiety and Depression Scale* (HADS) was developed to identify anxiety disorders and depression among patients. It is divided into an Anxiety subscale and a Depression subscale, both of which contain seven intermingled items. Each item is rated on a scale of 0 (best status) to 3 (worst status) [9].

#### Safety assessments

To assess the safety of SGJP, we will perform the following tests on participants at the screening phase (baseline) and after treatment (week 8): routine blood, routine feces, routine urine, liver and kidney function, and electrocardiography.

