#### Data collection

We will collect basic data from each patient including their characteristics and past history of cancer, outcomes, and safety assessment data at baseline and follow them up at 2, 4, and 8 weeks (Table 2).

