**Table 2 Tab2:** **Study visits**

	**Visit 1**	**Visit 2**	**Visit 3**	**Follow-up**
	**Baseline**	**Week 2**	**Week 4**	**Week 8**
Inclusion/Exclusion criteria	**×**			
Informed consent	**×**			
History/Demographics	**×**			
RPFS	**×**	**×**	**×**	**×**
ECOG-PS	**×**	**×**	**×**	**×**
SRSS	**×**	**×**	**×**	**×**
HADS	**×**	**×**	**×**	**×**
Safety assessment	**×**		**×**	
Adverse events		**×**	**×**	**×**
Combined medication		**×**	**×**	**×**

*Abbreviations*: ECOG-PS Eastern Cooperative Oncology Group Performance Status; HADS, Hospital Anxiety and Depression Scale; RPFS, Revised Piper Fatigue Scale; SRSS, Self-Rating Scale of Sleep.

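### The laboratory and ECG safety tests are set at week 8 in the text but at week 4 in Table 2, and week 8 falls four weeks after the last dose

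*Protocol article*

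**What the plan says.** Two places in the protocol article give a visit for the same tests.

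- **Safety assessments** lists routine blood, feces and urine tests, liver and kidney function and electrocardiography. It sets them "at the screening phase (baseline) and after treatment (week 8") and names no other time.
- **Table 2** has a row labelled "Safety assessment", marked under Visit 1 (baseline) and Visit 3 (week 4). The week 2 and week 8 cells are empty.

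Note 5 of the Figure 1 legend shows that both places mean the same procedure: "Safety assessment: routine blood test, routine feces test, routine urine test, liver and kidney function tests and electrocardiogram".

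The treatment timeline is not in doubt. Study design gives "a 4-week treatment period and a 4-week follow-up period". Intervention states "The intervention period will be over 4 weeks" and then "After 4 weeks on the prescribed medication, the patients will stop taking SGJP or placebo for another 4 weeks".

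Data collection says that investigators will collect the data at baseline and "follow them up at 2, 4, and 8 weeks (Table 2"), which makes Table 2 the reference for the visit schedule.

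**The concern.** One procedure has two schedules that agree only on baseline. The text describes week 8 as falling after treatment. That is literally true, but week 8 is the end of the off-drug period, not the end of dosing.

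A centre that works from the text takes its only post-baseline laboratory and ECG values after four weeks without study medication. An asymptomatic change in, say, liver or kidney function that arose on treatment and resolved after stopping would leave no trace in the scheduled tests. Such changes are what routine tests are there to catch, because adverse-event recording depends largely on symptoms. Readers also cannot judge the expected toxicity from the composition, since three of the six herbs are not disclosed.

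Recruitment is under way at three centres (Study design, Trial status). If centres read different parts of the document, they could test at different visits, and the safety values could not be pooled cleanly.

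**Working it through.** **Step 1: is the Table 2 entry read correctly?** The column positions were compared with those of other rows. RPFS has four marks, one per visit. The row "Adverse events" has an empty baseline cell followed by marks at weeks 2, 4 and 8. Against that layout, the second mark of the safety row falls under week 4 and the week 8 cell is empty. The mismatch does not come from text extraction.

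**Step 2: the two schedules side by side.**

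| | Safety assessments text | Table 2 |
|---|---|---|
| Baseline | yes | yes |
| Week 2 | no | no |
| Week 4 | no | yes |
| Week 8 | yes | no |
| Time since last dose at follow-up test | 8 − 4 = 4 weeks (about 28 days) | 4 − 4 = 0 weeks |

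**Step 3: how many patients are involved?** Sample size gives 118 patients and 15% attrition. That leaves 118 × 0.85 = 100.3, or 59 × 0.85 = 50.15 per arm. About 50 SGJP patients would be tested. Under the text, none of them has a scheduled value from the 28-day dosing period.

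**Step 4: what could be missed (illustration only).** Let *p* be the share of SGJP patients with an asymptomatic abnormality at week 4, and *f* the share of those abnormalities still present at week 8. Neither figure is in the document; both are assumptions. With *n* = 50:

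- chance of seeing at least one case at week 4: 1 − (1 − *p*)^50
- chance of seeing at least one case at week 8: 1 − (1 − *pf*)^50

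For *p* = 5%, week 4 gives 1 − 0.95^50 = 0.923. Week 8 with *f* = 50% gives 1 − 0.975^50 = 0.718.

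| *p* | Week 4 | Week 8, *f* = 0% | *f* = 25% | *f* = 50% | *f* = 100% |
|---|---|---|---|---|---|
| 2% | 64% | 0% | 22% | 40% | 64% |
| 5% | 92% | 0% | 47% | 72% | 92% |
| 10% | 99% | 0% | 72% | 92% | 99% |

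The grid uses the same *n* at both visits, because the article gives only one overall attrition figure. It counts only abnormalities already present at week 4, so by construction week 4 can never do worse than week 8.

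**The case against.** The case for treating this as trivial is that Table 2 is the declared schedule. If the centres use it, testing falls at the end of dosing and the only fault is a wrong number in one sentence. Efficacy, power and error rates do not change. Adverse events are collected at weeks 2, 4 and 8 either way.

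There is also a case that week 8 was meant. The text says after treatment, which week 8 is. The Intervention section ends with a clinical evaluation following the off-drug period. Data collection names safety data in a sentence that also mentions follow-up at 2, 4 and 8 weeks. On that reading, moving the tests to week 4 would remove an intended off-drug check.

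Finally, the detection grid rests on invented incidences, and its week 8 results run from 0% up to equality with week 4, so it does not fix the size of the problem.

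Much of this stands. Which entry is wrong is an inference, Figure 1 is not available to settle it, and the grid is illustrative only. It does not remove the contradiction. The clinical evaluation in the Intervention section names no laboratory tests. Data collection lists all data types together and refers back to Table 2; read literally, it would add a third timing for the safety tests. The rule as written in the Safety assessments section would, if followed, leave the dosing period without a single scheduled laboratory or ECG value.

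**Conclusion.** The contradiction is real and should be corrected. The document gives two visits, four weeks apart, for the only post-baseline laboratory and ECG tests. The text version places them about 28 days after the last dose. That gap follows from the document alone.

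The practical consequence depends on which schedule the centres use, and the document does not show this. Under Table 2 there is no gap during dosing. Under the text, silent changes that resolve within four weeks of stopping go unseen. How often that would happen depends on incidence and persistence, which are unknown here. The effect is confined to asymptomatic laboratory and ECG findings; the RPFS comparison is untouched. The existence of the mismatch is certain. That week 8 is the erroneous entry is only probable.

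**What to change.** In the Safety assessments section, change the post-treatment visit from week 8 to week 4 so that it agrees with Table 2. Check that Figure 1 shows the same visit, and confirm the week 4 schedule in writing to the three centres. If the investigators did intend an off-drug check, they should keep week 4 and add week 8 in both places.

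The correction costs one sentence and a short message to the centres, and adds no procedure to Table 2. Its small downside is that, with week 4 alone, no laboratory or ECG value is taken after the 4 weeks off drug, so delayed or persisting changes are not measured. Keeping both visits would remove that downside at the price of one further round of tests per patient.

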#### Sample size

Based on our previous study, we have baseline data from Chinese breast cancer patients with CRF in Beijing, China [12]. Although the study was published in a Chinese journal, we considered it is the most factual data. RPFS was the primary outcome in our previous study. The planned sample size is 118 patients with an anticipated 15% attrition rate. With this sample size, there will be in excess of a 95% power and a (1-side) 5% significance level in detecting treatment differences. The standard deviation is 1.27. The study was planned to detect a one-unit difference in change scores between the two groups.

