#### Randomization and blinding

Eligible patients will be randomized into the groups SGJP and placebo (P) in a 1:1 ratio for a target total of 118 patients. Patients will be randomized in blocks of four by **Statistical Analysis System** (SAS). This will be a double-blind study in which the participants and investigators are blinded. The patients will receive granules either with SGJP or placebo. These granules have the same taste, appearance, and color.

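### The claim of more than 95% power rests on an SD of 1.27 not identified as a score SD or a change SD; a baseline-adjusted analysis would largely remove the dependence

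*Protocol article*

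**What the plan says.** All planning inputs stand in one paragraph of the protocol article, under Sample size.

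- Source: "Based on our previous study, we have baseline data from Chinese breast cancer patients with CRF in Beijing, China". The paragraph adds that "RPFS was the primary outcome in our previous study".
- Variability: "The standard deviation is 1.27". It does not say whether this belongs to a baseline score, a follow-up score or a change.
- Effect: "The study was planned to detect a one-unit difference in change scores between the two groups".
- Size: "The planned sample size is 118 patients with an anticipated 15% attrition rate", allocated 1:1 according to Randomization and blinding.
- Claim: "there will be in excess of a 95% power and a (1-side) 5% significance level in detecting treatment differences".

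No correlation between baseline and follow-up RPFS is given. The Analysis section applies Student's t-test to the fatigue change scores at each time point, with no adjustment for baseline. It sets the threshold at P < 0.05 without saying whether the test is one- or two-sided. The Study visits table shows RPFS collected at baseline and at weeks 2, 4 and 8.

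**The concern.** The spread of RPFS between patients at one visit and the spread of within-patient change are different quantities. A t-test on change scores depends on the second. The only kind of data that the paragraph names as its source is baseline data, which describe the first. The two SDs coincide, with equal SDs at both visits, only when the baseline/follow-up correlation is exactly 0.5.

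The stated power can therefore be read in two ways, and the reader cannot tell which was meant. On one reading it is comfortably met. On the other it depends on a correlation that the plan does not give, and a low correlation would take the planned test below 95%.

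**Working it through.** **Inputs.** From Sample size: difference 1 RPFS unit, SD 1.27, 118 patients, 15% attrition, one-sided 5%. From Randomization and blinding: 1:1 allocation. Evaluable patients: 118 × 0.85 = 100.3, so 50 per arm. The correlation (rho) and the follow-up SD are not in the document and are varied below as assumptions.

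**Power formula.** Noncentral t with noncentrality = 1 / (SD × √(2/50)) and 98 degrees of freedom.

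**Step 1: reproduce the plan's figure, taking 1.27 as the SD of change.** Noncentrality = 1 / (1.27 × 0.2) = 3.94. Power is 98.8% one-sided and 97.4% two-sided. The claim of more than 95% reproduces.

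**Step 2: take 1.27 as the SD of the score at each visit.** Then SD of change = 1.27 × √(2(1 − rho)).

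| rho | SD of change | Power, one-sided | Power, two-sided |
|---|---|---|---|
| 0 | 1.796 | 86.9% | 78.7% |
| 0.2 | 1.606 | 92.6% | 86.9% |
| 0.3 | 1.503 | 95.1% | 90.9% |
| 0.4 | 1.391 | 97.3% | 94.5% |
| 0.5 | 1.270 | 98.8% | 97.4% |
| 0.6 | 1.136 | 99.7% | 99.2% |

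Solving for 95% power gives a largest tolerable SD of change of 1.509 one-sided and 1.373 two-sided. From rho = 1 − SD² / (2 × 1.27²), these correspond to rho of 0.294 and 0.415, that is, about 0.30 and about 0.42.

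**Step 3: ANCOVA on the follow-up score with baseline as covariate.** The residual SD is SD_follow-up × √(1 − rho²). Compare the two variances:

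variance of change − residual variance = (SD_base² + SD_fu² − 2 rho SD_base SD_fu) − SD_fu²(1 − rho²) = (SD_base − rho SD_fu)²

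This is never negative. For any pair of SDs and any rho, ANCOVA is at least as efficient as the change-score test, apart from one degree of freedom for the slope (97 in place of 98).

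- If 1.27 is the SD of change, the residual SD is at most 1.27.
- If 1.27 is a score SD and the follow-up SD is no larger, the residual SD is again at most 1.27.
- In both cases ANCOVA power is at least 97.4% two-sided with 50 per arm.

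**Step 4: where that bound fails.** It fails if 1.27 is a score SD and the follow-up SD is larger. With baseline SD 1.27 and an assumed follow-up SD of 1.5:

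| rho | ANCOVA residual SD | ANCOVA, two-sided | SD of change | Change-score test, two-sided |
|---|---|---|---|---|
| 0 | 1.500 | 91.0% | 1.965 | 71.2% |
| 0.3 | 1.431 | 93.3% | 1.649 | 85.1% |

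At an assumed follow-up SD of 1.8, ANCOVA power is 78.5% at rho 0 and 82.2% at rho 0.3.

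**The case against.** A reader might infer that 1.27 is the baseline SD, wrongly used as an SD of change, and that the trial is underpowered. The document does not support that. It never labels 1.27. The earlier study had RPFS as its primary outcome and could have supplied an SD of change, and the sentence straight after the SD speaks of change scores. The cited report would settle the matter but is not at hand. No arithmetic error has been shown: on the favourable reading the stated power reproduces.

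The shortfall on the other reading should not be exaggerated either. The planned level is one-sided, for which a correlation of about 0.30 suffices. A correlation of 0 is an extreme case for the same scale in the same patients 2 to 8 weeks apart. The two-sided column matters only because the Analysis section does not state the side, which is a separate question.

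The entry rule of RPFS ≥ 4 can be argued to lower the correlation by narrowing the baseline range. The document does not say whether the earlier sample was selected in the same way, so this cannot be quantified. The same rule could also leave the follow-up SD above the baseline SD, which is why ANCOVA power cannot be guaranteed at 97% for every correlation.

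Finally, an unadjusted t-test on change is valid under randomization, and a condensed article need not show the derivation of its SD. Both points stand. The case for ANCOVA is efficiency: it removes most of the dependence on the missing correlation, using data already planned.

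**Conclusion.** The claim of more than 95% power is conditional on what 1.27 measures; it is not shown to be false. It holds with room to spare (98.8% one-sided) if 1.27 is the SD of change. If 1.27 is a single-visit SD, equal at both visits, it holds only from a correlation of about 0.30 one-sided or about 0.42 two-sided, and one-sided power falls to about 87% at correlation 0. These figures assume 50 evaluable patients per arm and a true difference of one unit. A follow-up SD above 1.27 would raise the correlation needed. Nothing here shows that 118 patients are too few. The point is worth acting on because a small change to the analysis makes the power far less sensitive to an input that the plan does not give.

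**What to change.** 1. **Analysis:** replace the unadjusted t-test on RPFS change scores with a comparison of RPFS between groups by ANCOVA adjusted for baseline RPFS.
2. **Sample size:** state whether 1.27 is the SD of a score (and at which visit) or the SD of change.
3. **If it is a score SD:** restate power for the chosen test with the assumed correlation. Claim at least 97% two-sided power for ANCOVA only with the condition that the follow-up SD is no larger than 1.27, and show a less favourable case alongside, such as about 91% at an assumed follow-up SD of 1.5 and correlation 0.

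**Cost:** no extra patients, visits or measurements, since baseline RPFS is already collected. ANCOVA uses one degree of freedom. Because recruitment has begun, the change of analysis should be recorded as a dated amendment before unblinding. The restated power may look less favourable than the present claim if 1.27 proves to be a score SD.
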